### Assessment procedure

According to the behavioral framework, direct measures are preferred to psychometric inventory when possible. In any case, to deepen the understanding of mechanisms of change, psychometric measures were included. Participants will be asked to complete all study measures before randomization. Follow-up repeated measures assessment will be completed on all study participants 6 weeks later (post-treatment) and at 3, 6, and 12 months follow-up.

Demographic data such as gender, age, marital status, level of education, and employment status will be assessed in order to control for these potential confounders, checking also for biological indicators of risk—obesity, according to WHO criteria, with a BMI of 30 or more [67].

Primary outcome is physical activity as assessed continuously by wearable technology. Activity trackers will collect data, by direct measurement, of daily steps, physical activity, sleep, and food journal with the self-report app connected with the wearable device. Medical data and additional diagnoses (e.g., diabetes) that may confound results will be retrieved from clinical records.

Participants in both groups will provide a history of any psychological treatment or counseling to assess potential familiarity with mindfulness and acceptance-based therapies. A range of physiological and psychological outcome measures will assess the following: modifiable risk factors and recommended lifestyle dietary habits with the Mediterranean Diet Score [73], physical exercise with the International Physical Activity Questionnaire - Short Form (IPAQ-SF) [57] and the Acceptance and Action Questionnaire for Exercise (AAQ-EX) [85]. We also collect data about psychological well-being and quality of life (PGWBI) [47, 62, 85] and psychological flexibility (AAQ-II) [4, 49], a core process directly targeted by ACT interventions and involved as a mediator for well-being [53]. Adjusted change scores for all the outcome measures will be calculated in order to assess the ability of the interventions to produce changes over time.

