**Methods/design:**

A randomized clinical trial combining single-subject studies and a four-arm group design will be conducted to compare the effect of the current standard in obesity treatment to Acceptance and Commitment Therapy (ACT) and wearable technology at different times, before starting intervention, at the end, and at follow-up visits of 3, 6, and 12 months measuring changes over time of physical activity and psychological well-being.

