## Methods

### Study design

Recently the Oxford Centre for Evidence-Based Medicine (http://www.cebm.net/) has established that the level of scientific evidence of single-subject experimental designs (when some conditions are respected) has a rank that is similar to that of systematic reviews and just below that of a meta-analysis. Additionally the single-subject design is considered to have a higher ranking than the more conventional intergroup design often used for randomized clinical trials [51]. In the present study we integrate an experimental single-subject design that is repeated in multiple baselines. For the study an ample sample is available, and a significant number of data points is taken into account. This is made possible by the use of information technology, with activity trackers/wearables, which allow individual, continuous, and constant data collection.

This data analysis strategy is being performed with the intention-to-treat (ITT) method. This specific choice was adopted with two main purposes: maintaining similar treatment groups apart from randomization, and allowing non-compliance and deviations from the clinicians and researcher’s policy, keeping most of the possible exceptions under control. The continuous sampling and data collection, made possible mainly by a technological system of automatic devices, makes the use of a large sample of subjects possible. Moreover, it allows an experimental analysis of the participants even with the methodology of the comparison between randomized groups. For the side of group analysis this study is a small size RCT, with four different experimental conditions, depending on two different independent variables, each on two levels (present or absent), with a classic 2 × 2 design factorial. For every condition all the participants of the study follow the same inpatient, 4-week rehabilitation program followed by a 16-week outpatient phase. Psychometric and direct measures are collected during both the inpatient and outpatient phases, and at follow-up at 3, 6, and 12 months.

The experimental conditions are as follows:Gold Standard Intervention plus Activity Tracker WITHOUT FeedbackGold Standard Intervention plus Activity Tracker WITH FeedbackACT-Based Intervention plus Activity Tracker WITHOUT FeedbackACT-Based Intervention plus Activity Tracker WITH Feedback

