### Gold Standard Intervention plus Activity Tracker WITH Feedback

#### Behavioral change condition with activity tracker

In this experimental condition, participants will be provided the same rehabilitation program for the 4-week inpatient phase as in the control condition. In addition, for these subjects we will implement a stepped protocol using wearable devices/activity trackers to collect information about daily physical activity and providing meaningful and informative feedback. The additional procedure starts during the inpatient phase with delivery and explanation of the use of the wearable devices. In this meeting, longer than the one described for the control condition, experimenters provide information, set individualized goals, and explain the feedback to be delivered by the electronic wearable devices after the end of the inpatient phase. All subjects allocated to this condition will be clustered by date of entrance in the program; then, for each cluster, the length of the baseline phase will be randomly assigned. According to these allocations, the wearable device will start to provide feedback at different times for each participant in the cluster, to directly check the effect of contingent and informative feedback, one of the two independent variables of the study, on the daily level of physical activity, our primary outcome and dependent variable. The stepped protocol includes automatically generated feedback for achieving individualized goals in physical activity or related healthful habits. If the goal is missed one day, a daily report is automatically sent, but if any participant misses repeatedly, the individualized goal researchers provide an individualized contact by text message or e-mail.

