### Randomization procedure

Using a double-blind procedure, we will randomly assign all of the participants to one of the four groups. The randomization scheme will be generated using the website Randomization.com (http://www.randomization.com). Randomization and follow-up assessments will be administered by independent practitioners blind to the research hypotheses and condition assignments. The G*Power software (v3.1.9.2) [35, 36] was used to compute the minimum sample size required to conduct this study. All of the participants will be assessed with the Psychological General Well-Being Index (PGWBI) [47, 62, 85] five times: (1) at admission to the clinic, (2) at discharge, (3) at 3 months follow-up, (4) at 6 months follow-up, and (5) at 12 months follow-up. Thus, the *experimental condition* is considered as a between-group variable, and *time* is considered as a within-subject variable. The a priori statistics (partial η^2^ and correlation between measures) were computed by examining previous longitudinal studies using the PGWBI in subjects with obesity [9, 65]. The a priori partial η^2^ was set to assume a value of 0.015 (small effect size) [26, 30], the type I error (α) rate was set at 0.05 (two-sided), the power (1 – β) was set at 0.95 [26], and the a priori correlation between repeated measures was set at 0.50. Finally, sphericity was assumed. G*Power showed that there is a 95% chance to correctly reject the null hypothesis of no significant effect with an overall sample of 168 participants, 42 subjects for each group.

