### Statistical analysis

As this study combines group design with different single-case design or, more in detail, randomly assigned multiple baseline design clustered by sub-sequential recruitment. Following methodological guidelines of RCT, the implementation of statistical analysis is linked to synergies that we can not previse at this point.

Statistical analyses will be performed using the R software [86]. Preliminary analyses will be carried out to assess the assumptions of parametric statistics; in case of violations, robust methods or data transformation will be used. Direct collected data (steps, weight, etc.) will be analyzed with an ITT approach with dropouts assumed to have regained 0.3 kg per month, an assumption already used in previous studies [16]. Dropouts will be excluded from the study.

The analysis of variance (ANOVA) will be used to examine between-group differences for all the primary and secondary outcomes at all time-points, focusing on the change in the scores. Corrected effect sizes (Hedges’ *g*) and 95% confidence interval (95% CI) will be calculated for both between-group and within-group differences.

Moreover, growth curve model analysis with a group variable (between conditions) will be used to evaluate the average growth from the baseline to 12 months after treatment for all of the outcome variables as performed in previous studies [52]. Moderation and meditational analysis will be implemented as more advanced statistical models. All data analyses will be performed using the Statistical Package for the Social Sciences (version 16.0; SPSS, Inc., Chicago, IL).

In addition, considering that the present study combines different single-case designs, more detailed randomly assigned multiple baseline designs clustered by sub-sequential recruitment, and a group design following methodological guidelines of RCTs, the implementation of statistical analysis is linked to synergies that we cannot previse at this point. For the single-case design, we use a multiple-baseline procedure with the same number of data points for all the subjects assigned to a cluster. In each multiple-baseline cluster we randomly assign the length of the baseline and, consequently, of the treatment. Detailed visual inspection and graphical analysis will be use, followed by a randomization test to ensure statistical power to the visual analysis [37, 38].

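### The second assessment is set at discharge in one section and at 6 weeks, labelled post-treatment, in another; both fall 14 to 16 weeks before the 20-week programme ends

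*Protocol article*

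**What the plan says.** The protocol article describes the second of five assessments in three places.

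- Assessment procedure: baseline comes first ("Participants will be asked to complete all study measures before randomization"), and then "Follow-up repeated measures assessment will be completed on all study participants 6 weeks later (post-treatment) and at 3, 6, and 12 months follow-up".
- Randomization procedure, for the PGWBI: "1) at admission to the clinic, (2) at discharge, (3) at 3 months follow-up, (4) at 6 months follow-up, and (5) at 12 months follow-up".
- Abstract, Methods/design: "before starting intervention, at the end, and at follow-up visits of 3, 6, and 12 months".

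Study design gives all arms a "4-week rehabilitation program followed by a 16-week outpatient phase" and names follow-up separately from both phases.

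The intervention sections put active treatment in the outpatient phase. In the feedback arm, staff "explain the feedback to be delivered by the electronic wearable devices after the end of the inpatient phase", and the start of feedback is then staggered at random within each cluster. The ACT arm has monthly remote sessions and weekly messages after hospitalisation. The combined arm receives tracker feedback during the 16 weeks.

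For the follow-up clock, the only worded origin is under Statistical analysis, where the growth curve model covers "average growth from the baseline to 12 months after treatment". The same section applies ANOVA to change scores at every time point.

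**The concern.** The Background argues that gains are lost once the treatment setting is withdrawn, so the trial has to keep values taken during treatment apart from values taken after it. As written, a value taken less than a third of the way through the programme would be reported as the post-treatment result. None of the listed visits is fixed at the end of treatment.

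The label matters most for the feedback factor, one of the two factors in the 2 × 2 design. Device feedback has not begun at discharge and has barely begun at week 6, so a between-arm difference at that visit cannot stand for its end-of-treatment effect.

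The label also affects the follow-up clock. A count of months after treatment depends on when treatment is taken to end, and the article attaches the post-treatment label to week 6.

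**Working it through.** **Inputs.** Inpatient phase 4 weeks and outpatient phase 16 weeks (Study design). Second assessment at discharge (Randomization procedure) or 6 weeks after baseline (Assessment procedure). Feedback starts after the inpatient phase (feedback arm). Assumption: baseline is at admission, week 0, which agrees with the first PGWBI assessment under Randomization procedure. One month = 365.25 / 12 / 7 = 4.35 weeks.

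**The plan's own sample size, as a check.** With partial η² = 0.015, f² = 0.015 / 0.985 = 0.01523. For a group-by-time interaction with 4 groups, 5 assessments, correlation 0.50 and N = 168, the noncentrality is 0.01523 × 168 × 5 / (1 − 0.50) = 25.6 on 12 and 656 degrees of freedom. Power is 0.944, against the stated 0.95. The minimum N is 173, or 176 in equal groups; with f rounded to 0.125 these become 169 and 172. The stated 168 is accepted as consistent with five assessments. The timing point does not dispute it.

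**End of programme.** 4 + 16 = week 20.

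**Second assessment.**
- Discharge: week 4, which is 4/20 = 20% of the programme and 20 − 4 = 16 weeks before its end.
- Six weeks after baseline: week 6, which is 6/20 = 30% of the programme and 20 − 6 = 14 weeks before its end.
- The two definitions differ by 6 − 4 = 2 weeks.
- Device feedback received by then: none at week 4; at most 6 − 4 = 2 weeks at week 6, less any randomly assigned baseline period.
- Bound on the assumption: if baseline were as late as the end of the inpatient stay, the visit would be at week 4 + 6 = 10, still on treatment, with at most 10 − 4 = 6 weeks of feedback.

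**Follow-up visits, in weeks from admission, by origin.**

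| Origin | 3 months | 6 months | 12 months |
|---|---|---|---|
| Admission (week 0) | 13.0 | 26.1 | 52.2 |
| Discharge (week 4) | 17.0 | 30.1 | 56.2 |
| 6-week visit (week 6) | 19.0 | 32.1 | 58.2 |
| End of programme (week 20) | 33.0 | 46.1 | 72.2 |

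The 3-month value precedes week 20 under three of the four origins. The 6- and 12-month values follow week 20 under all four. If the origin is week 20, nothing is scheduled between week 4 or 6 and week 33, a gap of 29 or 27 weeks that contains the end of treatment.

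**Does an early visit weaken the group-by-time test?** For a fixed error variance, the noncentrality is proportional to the sum over visits of (d_t − mean d)², where d_t is the group difference at visit t. Assume a constant effect d once feedback has started.
- Second visit unexposed, pattern (0, 0, d, d, d), mean 0.6d: 2 × 0.36 + 3 × 0.16 = 1.20 d².
- Second visit fully exposed, pattern (0, d, d, d, d), mean 0.8d: 0.64 + 4 × 0.04 = 0.80 d².
- Second visit dropped, pattern (0, d, d, d), mean 0.75d: 0.5625 + 3 × 0.0625 = 0.75 d².

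Under this pattern the unexposed visit adds to the interaction test.

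**The case against.** The strongest reply is that this is a labelling matter. Steps, the primary outcome, are recorded continuously, so an end-of-treatment value exists whatever the visits are called. The single-case analysis follows the randomised baseline length, not the visit. The 6- and 12-month values are after treatment under any origin. The SPIRIT schedule figure is not shown and may state the origin, and the abstract's wording is a condensed phrase that need not be a third schedule. All of this stands and limits the harm to the questionnaire measures and to the tracker window that is called post-treatment. It does not remove the mismatch between the two Methods sections, or make week 6 the end of a 20-week programme.

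Reading treatment as the hospital stay alone does not help. Six weeks does not match four, and much of the experimental treatment comes after discharge.

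A reader might infer more than the documents support:

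- *That the 3-month value is certainly on treatment.* A list of visits in order states no origin. The one worded origin, together with follow-up being named apart from both phases, favours week 20, which puts the 3-month visit at week 33.
- *That the feedback comparison at discharge must be null.* The feedback arm has a longer device meeting in hospital, at which individual targets are set, so the arms already differ. Only feedback from the device is absent. The visit also follows the four inpatient ACT sessions and is informative for that factor.
- *That the early visit dilutes the condition-by-time test, so feedback should be tested only later.* The sums above point the other way under a constant effect: 1.20 d² with the visit and 0.75 d² without it.
- *That the article calls discharge post-treatment.* It does not; that label is attached only to the 6-week visit. The conflict is that both descriptions fill the same slot in the sequence.

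**Conclusion.** The point holds as an inconsistency and a wrong label. The second assessment has two dates, about week 4 and week 6, and both are on treatment, 16 and 14 weeks before the programme ends. With baseline at admission, device feedback has run for zero to about 2 weeks at that visit, although goal setting has begun. No listed visit is fixed at week 20. The origin of the follow-up visits is under-specified in the text: the 3-month value is on treatment if counted from admission, discharge or the 6-week visit, and off treatment if counted from week 20.

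This rests on two assumptions: baseline at admission, and the outpatient phase counting as treatment, as the intervention sections describe it. It should be fixed because it determines which value is reported as the post-treatment effect. It does not threaten the sample size or the ability to study lasting effects at 6 and 12 months.

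**What to change.** Reconcile the abstract, Study design, Randomization procedure, Assessment procedure and Statistical analysis.

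1. State every assessment in weeks from randomisation, and say when randomisation occurs relative to admission.
2. Choose week 4 or week 6 for the second assessment and label it discharge or interim.
3. Define post-treatment as the end of the outpatient phase, week 20. Take the step value from the continuous tracker record. For the questionnaires, add one completion through the existing web platform.
4. Count 3, 6 and 12 months from one stated origin consistent with Statistical analysis. If another origin is used, label the 3-month value as on-treatment.

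Keep the early visit in the analysis under its correct label. The cost is wording and at most one extra questionnaire. If that makes six assessments, the same effect size and correlation give power of 0.967 at N = 168, so no more participants are needed.

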### Psychotherapists and treatment fidelity

Motivational support and psycho-education will be supervised by experienced and certified psychotherapists from diverse backgrounds with specific training in CBT. The brief ACT intervention will be delivered by two psychotherapists with ACT and CBT background and formal training in ACT. They will receive monthly supervision by senior certified psychotherapists to ensure competent and uniform treatment delivery. A fidelity checklist, checked by a third, blinded therapist, will also be used for both treatments.

### Statistical analysis

As this study combines group design with different single-case design or, more in detail, randomly assigned multiple baseline design clustered by sub-sequential recruitment. Following methodological guidelines of RCT, the implementation of statistical analysis is linked to synergies that we can not previse at this point.

Statistical analyses will be performed using the R software [86]. Preliminary analyses will be carried out to assess the assumptions of parametric statistics; in case of violations, robust methods or data transformation will be used. Direct collected data (steps, weight, etc.) will be analyzed with an ITT approach with dropouts assumed to have regained 0.3 kg per month, an assumption already used in previous studies [16]. Dropouts will be excluded from the study.

The analysis of variance (ANOVA) will be used to examine between-group differences for all the primary and secondary outcomes at all time-points, focusing on the change in the scores. Corrected effect sizes (Hedges’ *g*) and 95% confidence interval (95% CI) will be calculated for both between-group and within-group differences.

Moreover, growth curve model analysis with a group variable (between conditions) will be used to evaluate the average growth from the baseline to 12 months after treatment for all of the outcome variables as performed in previous studies [52]. Moderation and meditational analysis will be implemented as more advanced statistical models. All data analyses will be performed using the Statistical Package for the Social Sciences (version 16.0; SPSS, Inc., Chicago, IL).

In addition, considering that the present study combines different single-case designs, more detailed randomly assigned multiple baseline designs clustered by sub-sequential recruitment, and a group design following methodological guidelines of RCTs, the implementation of statistical analysis is linked to synergies that we cannot previse at this point. For the single-case design, we use a multiple-baseline procedure with the same number of data points for all the subjects assigned to a cluster. In each multiple-baseline cluster we randomly assign the length of the baseline and, consequently, of the treatment. Detailed visual inspection and graphical analysis will be use, followed by a randomization test to ensure statistical power to the visual analysis [37, 38].

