
### The present study

Principal reasons for the long-term failure of obesity interventions are the lack of long-term sources of reinforcement for healthful habits acquired during the intensive treatment period [14, 31, 32]. The tradition of behavioral sciences has developed models of interpretation, explanation, and pragmatic operation supported by evidence of effectiveness and efficiency in the promotion of desired behaviors in various contexts, for example, smoke cessation [10, 81], pathological Internet use [69, 70], the ability to live with chronic diseases [6, 48, 66], and the promotion of safety behaviors in working environments [71, 88]. For this reason, behavior analysis in general, and in particular *contextual behavioral science*, can play a decisive role in the prevention of obesity and in the maintenance of the results achieved within short intensive protocols, usually held in hospitals. By modifying deeply rooted and long-term acquired habits, obese patients can obtain more psychological and physical health, reduce risk factors, and improve their overall health, wellness, and quality of life [53, 59] with benefits not only for the individual but also for his social environment. During rehabilitation patients affected by obesity are frequently in contact with contingencies extremely different from those occurring in their daily lives. During rehabilitation or hospitalization, contingencies are efficiently shaped to promote desired behaviors and decrease actions that are identified as dysfunctional, with both aversive and reinforcing contingencies. Later on, after the treatment, in the patient’s natural environment initially behaviors are maintained, but since they were reinforced in an environment that provides adequate contingencies, they often undergo a process of extinction consequently with cessation of reinforcement [79]. At the same time, outside the hospital, dysfunctional behaviors, such as avoiding physical activity and eating tasty food, are reinforced in a systematic and contingent way. This tendency to extinction of functional and healthful habits and reinforcement of dysfunctional habits leads, in the long term, to gaining of the weight lost laboriously, which also leads to lower levels of well-being [77]. Although the existing programs already provide protocol phases to be implemented once patients are home, often the patients fail to adhere to nutrition programs and planned activities. On the contrary, they return frequently to previous habits and show a high dropout rate at follow-ups [76].

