### Hypothesis, goals, and expected results

The project aims to promote a long-term change in lifestyle as part of a multidisciplinary intervention, in close collaboration with physicians, the service of clinical nutrition, and osteoarticular rehabilitation.

The main goal of this study is test the efficacy of combining behavioral change technologies through contingent and meaningful feedback provided by wearable devices with an intervention based on ACT, a well-studied psychological treatment developed in a contextual behavioral framework. The combinations of this approach should be feasible and efficient, compared with the gold standard treatment, and have lower costs. Four experimental conditions are provided: (1) usual care during hospitalization with programmed follow-up checks, (2) contingent feedback on daily life activities through activity trackers or stand-alone wearable devices, (3) stand-alone ACT-based intervention, (4) a combination of the previous two conditions: ACT-based intervention and activity tracker with feedback.

The primary outcome, or dependent variable, of the study is level of physical activity as collected by wearable electronic devices, a largely used parameter in scientific investigations [33, 68]. Other outcomes—for example, time of sleep—are collected by wearables, and others are provided by self-report through the web platform. The independent variable of the study is the type of treatment (ACT intervention and feedback provided by activity trackers). For the purpose of the study we collect data about daily steps and a workout log for each participant.

The intervention aims to help people in their everyday environment to more consistently keep the choices they have made and follow appropriate recommendations on diet and movement. The project is directed to participants in the multidisciplinary rehabilitation program at St. Joseph Hospital - Verbania, Istituto Auxologico Italiano, a private research institute that also works for the Italian national health system. The recruitment will take place progressively, and subjects will be randomized to the four experimental conditions set by the protocol. Data will be analyzed in different experimental single-subject over multiple-baseline designs [2, 8]. The subjects are also grouped according to the experimental conditions to allow statistical analysis of experimental intergroup designs, consistent with the approach of a randomized controlled trial (RCT).

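### Intention-to-treat and exclusion of dropouts are both specified, and the only dropout rule is in kilograms, so the ITT analysis of steps cannot be run as written

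*Protocol article*

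**What the plan says.** The Study design section sets the principle: "This data analysis strategy is being performed with the intention-to-treat (ITT) method". The reasons it gives are to keep the randomised groups comparable and to accommodate non-compliance and deviations.

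The Statistical analysis section repeats the principle for device and clinical measurements and attaches a rule for dropouts: "Direct collected data (steps, weight, etc.) will be analyzed with an ITT approach with dropouts assumed to have regained 0.3 kg per month". The following sentence is "Dropouts will be excluded from the study".

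The outcome at stake is not weight. Under Assessment procedure: "Primary outcome is physical activity as assessed continuously by wearable technology". Under Hypothesis, goals, and expected results: "For the purpose of the study we collect data about daily steps and a workout log for each participant".

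Two group analyses are named, and neither comes with a statement on how incomplete participants enter it: "The analysis of variance (ANOVA) will be used to examine between-group differences for all the primary and secondary outcomes at all time-points", and "growth curve model analysis with a group variable (between conditions) will be used to evaluate the average growth from the baseline to 12 months".

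On how common dropout may be, the background section on the present study says that patients in existing programs "show a high dropout rate at follow-ups". No rate is given for this trial.

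**The concern.** One sentence keeps dropouts in the analysis with an assumed value. The next takes them out. A statistician following the article cannot do both, and exclusion would defeat both reasons that the Study design section gives for choosing ITT.

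The assumed value is also in the wrong unit for the outcome that matters most. Steps are named first among the data that the rule covers, yet a monthly weight regain implies no step count. No other dropout rule for steps appears in the article.

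This matters because loss could well differ by arm and relate to activity. The control arm gets a tracker presented as a data collector without feedback. The other arms get feedback with individual messages, ACT sessions with weekly texts or e-mails, or both. A participant who stops wearing the device also stops supplying the primary outcome. If dropouts are then removed, the groups compared are no longer the groups randomised.

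**Working it through.** **1. The instructions side by side, applied to steps**

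| Instruction | Section | Can it be applied to steps? |
|---|---|---|
| Analyse by ITT | Study design; Statistical analysis | Only with a way of handling missing steps |
| Assume 0.3 kg regained per month | Statistical analysis | No, wrong unit |
| Exclude dropouts | Statistical analysis | Yes, but this contradicts ITT |

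The only dropout instruction that can be carried out for steps is the one that contradicts the stated principle.

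**2. Bias if dropouts are excluded (illustration; all inputs assumed)**

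Let p be the proportion lost in an arm, and let gap be the completer mean minus the dropout mean.

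- Overall mean = (1 − p) × completer mean + p × dropout mean = completer mean − p × gap.
- So completer mean = overall mean + p × gap.
- With equal true means and the same gap in two arms, false difference = (p1 − p2) × gap.

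| Difference in loss | Gap 1,000 steps/day | Gap 2,000 steps/day |
|---|---|---|
| 5 points | 0.05 × 1,000 = 50 | 0.05 × 2,000 = 100 |
| 20 points | 0.20 × 1,000 = 200 | 0.20 × 2,000 = 400 |

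The arm that loses more looks better, because more of its low walkers have been removed.

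Equal loss is not a safeguard. Suppose there is no true effect and the same proportion d is lost at both levels of one factor. Loss is random at one level and has correlation r with the outcome at the other. The completers' bias is then r × φ(z_d)/(1 − d) in SD units. With r = 0.3 (assumed):

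- d = 10%: 0.06 SD, and a two-sided 5% main-effect test rejects in 6.5% of trials.
- d = 20%: 0.3 × 0.280/0.80 = 0.11 SD, rejection 9.3%.
- d = 30%: 0.15 SD, rejection 12.7%.

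These rejection rates use 84 × (1 − d) participants per factor level.

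**3. Power if dropouts are excluded**

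Inputs from the article's sample size paragraph (Randomization procedure): partial η² = 0.015, α = 0.05, power 0.95, correlation 0.50, sphericity, 4 groups, 5 measurements, N = 168. No dropout allowance is stated.

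Formula (repeated-measures ANOVA, within-between interaction):

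- f² = 0.015/0.985 = 0.01523, so f = 0.1234.
- λ = f² × N × 5/(1 − 0.50).
- df1 = 3 × 4 = 12; df2 = (N − 4) × 4.

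The plan's own figure first: at N = 168, λ = 25.6, df2 = 656 and power = 0.944. The smallest N for 0.95 is 173, or 169 if f is rounded to 0.125. The stated 168 is therefore reproduced closely.

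| Excluded (assumed) | Analysed | λ | Power |
|---|---|---|---|
| 0% | 168 | 25.6 | 0.944 |
| 10% | 151 | 23.0 | 0.912 |
| 20% | 134 | 20.4 | 0.866 |
| 30% | 117 | 17.8 | 0.802 |

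This calculation is for the PGWBI. It says nothing direct about power for steps.

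**The case against.** The contradiction itself is hard to defend, but several stronger readings are tempting and the article does not support them.

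- **That the primary analysis is a completers analysis.** A reader might infer this, since exclusion is the only workable instruction for steps. But ITT is stated in two sections, and exclusion from the study may mean only that participation ends. Step data recorded before dropout could then enter the growth curve model. On that reading the handling of steps is undefined, not completers-only. This objection stands, so the conclusion is conditional.
- **That weight is filled in with one fixed value, making its standard error about 30% too small.** The rule is a rate of regain, naturally added to a participant's last weight, so imputed changes would vary between people. With 30% imputed (assumed), a ratio of √(0.7s²/n)/√(s²/(0.7n)) = 0.70 needs imputed changes with no variance. If they keep full variance the ratio is √0.7 = 0.84. Weight is also not the primary outcome.
- **That the rule fails for the questionnaires too.** It is limited to directly collected data. Silence on missing questionnaire scores is something an article may leave to the full protocol or analysis plan.
- **That the bias is known in size or direction.** The remark on high dropout describes existing programs. If extra contact retains participants, the control arm loses more and the bias runs against the interventions.

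A final defence is that an analysis plan would settle the matter. That does not answer the point: the article states incompatible rules, and a plan written from it would have to overrule one of them.

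**Conclusion.** Wrong as written. The article requires dropouts to be both kept and excluded, and its one dropout assumption cannot be applied to the primary outcome. That conclusion rests on the text alone and needs no assumption.

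The consequences are conditional on the exclusion sentence being followed. The false difference of about 50 to 400 steps/day depends on assumed differences in loss and assumed gaps in activity, and its sign depends on which arm loses more. The fall in power from about 0.94 to between 0.91 and 0.80 depends on an assumed 10 to 30% exclusion and applies to the PGWBI interaction test only. The contradiction should be resolved before outcome data are analysed, because it determines who is in the primary comparison.

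**What to change.** 1. Delete "Dropouts will be excluded from the study", or state that it means only the end of participation and not removal from the analysis.
2. Analyse every randomised participant in the allocated arm, using all step data up to the last record. Fit the growth curve model already planned as a likelihood-based mixed model under missing at random, and name it the primary group analysis of steps. The article does not now say that the model has mixed effects or that it takes precedence over the ANOVA.
3. Restrict the 0.3 kg per month assumption to weight, as a sensitivity analysis.
4. Add a sensitivity analysis for steps in which missing values are shifted from the model's prediction over a range stated in advance.

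The cost is a little more analysis work and a reliance on missing at random, which the sensitivity analysis in item 4 tests. No change to sample size or data collection is needed for these four items. Collecting step data after a participant stops treatment would be a separate change of conduct, with its own cost.
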